**Fig. 1 Fig1:**
[figure not shown]
Combinations of interventions

**Table 1 Tab1:** Flow diagram

	Study period					
	Selection visit	Randomization visit	Postrandomization visit			Emergency visit
Time point	T-1	T0	T0 + 1 yr	T0 + 2 yrs	T0 + 3 yrs	Between T0 and T0 + 3 yrs
Enrolment:						
- eligibility screen	X					
- informed consent	X					
- randomization		X				
Interventions:						
- caries management		X				If needed
- X-ray	X	X	X	X	X	If needed
Control of carious eviction with the SoproLife*®*		X				
assessment:						
- baseline variables	X	X				
- FDI criteria			X	X	X	X
- other data variables listed in the CRF			X	X	X	X

*FDI* FDI World Dental Federation, *CRF* case report form

**Fig. 2 Fig2:**
[figure not shown]
Flow chart

### Setting and participants

This study is being carried out in 13 academic hospitals and two private practices in France (study sites can be found at ClinicalTrials.gov; inclusion from February 2015 to July 2016).

Eligible patients, and their parent(s), if necessary, receive the study information. Informed consent forms are given to the patient and to the parent(s) of minor patients (age 8–18 years), before inclusion.

To be included in the trial, patients must 8–80 years old, able to receive dental care, covered under the national health coverage system, and have a mature permanent posterior tooth affected by a deep carious lesion. The tooth should have normal response to pulp sensitivity tests, without periapical pathology, and require direct restorative procedure. Exclusion criteria are not French-speaking, under guardianship or pregnant, have a pacemaker, or at risk of infectious endocarditis. Other exclusion criteria are severe periodontal disease (axial or high lateral mobility and/or pocket depth more than 5 mm), poor oral hygiene (patient with abundant plaque, i.e., plaque index = 3 according Silness and Loe plaque index) and allergy to any component of the materials used in the procedure. Teeth with excessive wear, carious cervical lesion, external or internal resorptions, or abutment for removable partial denture are not eligible. Exclusion criteria have been chosen to reduce loss of follow-up or modifications independent of the treatments studied.

Medications (painkillers, non-steroidal anti-inflammatory drugs) taken less than 8 days before or during the study must be reported.

No special concomitant care or intervention is prohibited after inclusion in the trial, except that concerning the included tooth.

### Sample size

According to a literature review [9, 34–42], 97 % and 90 % of success is expected for P and C dentin excavation strategies, respectively. A total of at least 464 patients would be needed for a bilateral test with an alpha risk of 5 % and a power greater than 80 %, supposing at 1 year 10 % of patients lost to follow-up as a ‘not to exceed’ value (calculated by nQuery Advisor 7.0) [43–45].

With the expected recruitment of each investigator, in order to reach the target sample size and respect the inclusion period of 18 months, this trial involves 15 centers. To encourage recruitment, the main investigator sends an encouraging text message after each inclusion and the center recruitment appears on the main page of the randomization website.

### Randomization

Randomization is performed using a computerized and centralized system via a specific website. A two-stage randomization process allows for integrating the two levels of randomization (i.e., the type of excavation and the nature of the adhesive). A minimization procedure is implemented to take into account the following prognostic characteristics: investigator, patient age (by age group), type of carious lesion (primary or secondary), location of the lesion (proximal or occlusal) and pulp exposure.

Because all patient and cavity characteristics must be entered in the electronic case report form (eCRF) before interventions are assigned, sequence concealment is secured.

### Implementation

The minimization algorithm was implemented by statisticians and methodologists independently of investigators. Patients are assigned to interventions arm by the investigators.

### Intervention

At the first visit, eligibility criteria are verified by an investigator. Information about the study is then given to the patient and the inclusion is formalized by the signing of the informed consent form.

A clinical examination is performed, then (1) pulp vitality is assessed with thermal (cold) and electrical methods (Elements Diagnostic Unit and Apex Locator®, Kerr Endodontique, Bioggio, Switzerland); and (2) bite-wing and retroalveolar radiographs are taken by using film-holders supplied by Kerr Endodontique. Bite-wing radiographs allow for assessing the depth of the lesion: no continuity between the carious lesion and the pulp chamber should be seen; and retroalveolar radiographs allow for determining the periapical index [46]. In case of multiple carious lesions, the lesion that best meets the inclusion criteria and allows for the best handling (easy access) is chosen. Other lesions will be further treated according to usual procedures and will not be entered in the study.

At the second visit, an investigator performs the tooth restoration. The tooth is anesthetized. The shade of the tooth-colored restoration is selected before isolation with the rubber dam. The first randomization is achieved. The superficial necrotic tissues and peripheral demineralized dentin are removed with complete excavation to avoid excavation close to the pulp. The bulk of the carious dentin is removed by using sterile round ceramic burs (Komet France, Paris, France) under water spray cooling and the final excavation with hand instruments. The excavation is controlled by use of an intraoral light-induced fluorescence camera (Soprolife®, Acteon Group, La Ciotat, France) and the corresponding image is registered. According to the manufacturer of the Soprolife® camera, infected carious tissues appear green-black in fluorescence. The infected/affected dentin interface emits bright red fluorescence in active lesions and dark red fluorescence in arrested lesions. The underlying dentin looks gray-green in fluorescence [47].

For cases under P excavation, the investigator stops excavating when the dentin close to the pulp appears bright or dark red after removal of the green-black infected dentin.

For cases under C excavation, the investigator stops excavating when the dentin close to the pulp appears gray-green after removal of the green-black infected dentin and removal of the bright or dark red infected/affected dentin interface.

With pulp exposure < 2 mm^2^ after C excavation, the exposed pulp is irrigated with chlorhexidine. Following hemostasis (within 5 minutes), a tricalcium silicate cement (Biodentine™, Septodont, Saint Maur des Fossées, France) is applied according to the manufacturer’s instructions. After complete cement setting (within 15 minutes), the cavity is restored following the same clinical procedures as for cases without pulp exposure.

With pulp exposure > 2 mm^2^ and/or no hemostasis, a root canal treatment is performed, and the case is considered a failure for randomization 1 but not randomization 2.

Cases undergo randomization 2 to determine the adhesive system: Clearfil™ SE Bond (Kuraray Europe) or Clearfil™ SE Protect (Kuraray Europe) (i.e., TA and AA, respectively). Enamel and dentin are prepared according to the manufacturer’s instructions. The tooth is restored by using the Gradia® Direct Flo and Gradia® Direct Posterior composite resin (GC Europe N.V., Leuven, Belgium) in accordance with the manufacturer’s instructions and if necessary a matrix system (Kerr Restauration, Bioggio, Switzerland). The photo-polymerization steps involve use of a LED curing light (Demi™ Ultra, Kerr Restauration, Bioggio, Switzerland). Then, a bite-wing radiograph is taken as a control.

Various strategies are implemented to improve adherence to intervention protocols: the investigator must submit the fluorescence image obtained after caries removal as well as the control radiograph to the randomization website. He must also indicate the adhesive applied.

### Outcome measures

Cases are considered successful if each of the following five FDI World Dental Federation (FDI) criteria has a final score ≤ 3: material fracture and retention, marginal adaptation, radiographic examination (including apical pathologies), postoperative sensitivity and tooth vitality, and recurrence of carious lesions [48, 49]. A score of 4 or 5 indicates that reintervention is necessary and, therefore, the case is classified as a failure in the context of the study. Criteria are scored at 1, 2, and 3 years’ postintervention by two blinded independent trained evaluators. Study assessing the agreement between evaluators for FDI criteria is ongoing. In cases of emergency visits, FDI criteria will be scored by the investigator.

For the primary objective (P versus C excavation) and the main secondary objective (AA versus TA), the outcome will be the success (yes/no) at 1 year, as defined previously.

For the first secondary objective (identification of factors predicting success at 1 and 3 years), the following candidate factors will be investigated: postoperative pain, patient age, type of carious lesion (primary or secondary), location of the carious lesion, and pulp exposure.

For the second secondary objective (description of the consequences of treatment failure and side effects per treatment arm), the following events will be considered: total number of needed visits, number of endodontic treatments, and number of avulsions.

### Data collection methods

Trial data are collected in an eCRF. To promote data quality, investigators, and evaluators (examiners), who will assign scores, are trained in the FDI criteria by means of the e-calib web-based software (www.e-calib.info) and group training sessions. Two independent evaluators will perform the follow-up examinations. If disagreements occur during the evaluations, evaluators will have to reach consensus. Data collection forms can be found in the trial protocol as well as on the randomization website. To promote participant retention and complete follow-up, each patient will receive 90€ on completion of the trial as compensation for attending the follow-up appointments.

### Data management

Data are entered by investigators and evaluators on the eCRF. Fields include range checks for data values. Fields cannot be left blank.

Interactive data controls will be applied for value ranges and presence of and between-form coherence. Data will be kept anonymous, with high-level security storage, with encryption of all data transfers, in compliance with French regulatory and European Clinical Research Infrastructure Network (ECRIN) requirements.

### Statistical methods

The statistical unit for analysis will be the tooth. Only one tooth per patient will be included and treated according to the protocol. The demographic and clinical characteristics of patients and treated teeth will be described for both treatment arms with mean and SD or median and interquartile ranges for quantitative variables and number of subjects, and percentages for qualitative variables. The analyses will be performed according to the intention-to-treat principle.

To evaluate the primary objective, the probability of success in arms P and C at 1 year will be calculated and compared by Fisher’s exact test. The probability of success for each arm (0 for treatment failure and 1 for success, at 1 year) will be assessed by a hierarchical logistic model. This model accounts for the correlation related to the hierarchical structure of the data (several patients treated by one practitioner) as well as any possible inter-practitioner heterogeneity. The model will be adjusted on the type of adhesive (arm AA or TA) and on prognostic factors accounted for in the minimization scheme. If necessary, other adjustment factors might also be considered. In cases of patient non-compliance with follow-up visits, the last investigator’s assessment will be used in the analysis, if there is one.

All analyses related to the primary objective (Fisher’s exact test and the modeling approach) will initially include all patients with an available primary outcome as modified ITT. The number of patients to be included has been increased to account for missing outcomes. Then, three sensitivity analyses will be performed: the first according to the maximal bias approach (missing data considered as “success” in arm C and as “failure” in arm P), the second considering all missing data as successes, and the third considering all missing data as failures.

For the secondary objectives comparing efficacy (as defined for the primary objective) at 1, 2, and 3 years and between arm AA and arm TA at the three different times, similar analyses to those used for the primary objective will be performed. The probability of success for each criterion will be assessed and compared between arms by using the hierarchical logistic model described previously.

Candidate factors for subgroup analyses are patient age, type of carious lesion (primary or secondary), caries risk, lesion location, and pulp exposure. Subgroup analyses will be performed globally, then stratified by type of removal (C and P) and adhesive (AA and TA). In the model analysis, the interaction between a specific factor and the type of removal (arms C versus P) or the adhesive used (arms AA versus TA) will also be considered by its clinical relevance and in the descriptive analyses. The consequences of failure and side effects between arms will be assessed by a descriptive approach (range, median, and quartiles for quantitative variables, number and percentage for qualitative variables).

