## Methods/design

### Trial design

The Standard Protocol Items: Recommendations for Interventional Trials (SPIRIT) guidelines [33] have strictly been followed in the planning of this trial (Additional file 1).

This trial is a multicenter intention-to-treat randomized controlled superiority trial with parallel arms. Analysis of results will be performed according to the intention-to-treat principle. For the primary objective, only patients are blinded to the allocated intervention (partial or complete caries removal). For the secondary objective (type of adhesive), both patients and investigators are blinded. Outcome examiners and data analysts are always blinded.

Two successive randomizations are performed (allocation ratio 1:1): first, for the type of excavation (P versus C) and second, for the adhesive system (AA) versus TA. The second randomization is not performed for teeth requiring endodontic treatment after the first randomization.

The possible combinations of interventions are in Fig. 1, the flow diagram is mentioned on Table 1 and the flow chart of the study is in Fig. 2.

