All current recommendations (the SPIRIT statement) were taken into account for the design of the present clinical trial [33]. A complete factorial design would have allowed for exploring the interaction between the management strategies (P versus C excavation, and AA versus TA). However, the impossibility of randomizing the adhesive with endodontic treatment, expected to be more frequent with C excavation, led us to adopt a nested design with two distinct and successive randomizations. The tooth was chosen as the statistical unit, with only one tooth per patient, to ensure the independence between statistical units. If a split-mouth design had been chosen, finding patients with two cavities similar in depth would have been difficult. In terms of internal validity, the sources of bias are limited by the use of centralized randomization (selection bias), strict prospective data record and monitoring (information bias), and blinded patients and evaluators (performance and detection bias). However, because of the nature of the investigation, the investigators cannot be blinded.

The choice of assessment criteria is based on the 16 criteria for evaluating direct restorations published and approved by the FDI [48]. As suggested by Hickel et al., a selection of criteria was chosen to match the objectives of the study [49]. The focus was functional properties (material fracture and retention, marginal adaptation, radiographic examination) and biological properties (postoperative pain and tooth vitality, recurrence of carious lesions).

The clinical procedure is carried out under optimal conditions. One of the main points is that partial removal involves only the tissues close to the dental pulp. Indeed, the cavity margins should include no carious tissue so as to avoid the recurrence of the lesion at the tooth-restoration interface. Decay can reach different surfaces of the tooth, but the restoration must be single and unique to avoid any confusion during the evaluation step. For the same reason, the included tooth must be free of cervical carious lesion.

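### The model comparing partial with complete excavation adjusts on adhesive arm, which is undefined for teeth root-canal treated at the randomization visit, although the model is meant to include every patient with an outcome

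*Protocol article*

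**What the plan says.** All references are to the protocol article.

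- **Statistical methods**, on the hierarchical logistic model for the primary objective: "The model will be adjusted on the type of adhesive (arm AA or TA"), together with the prognostic factors used in the minimization. The next paragraph says that both Fisher's test and the modeling approach will first be run on all patients whose primary outcome is available, which it calls modified ITT.
- **Trial design**: "The second randomization is not performed for teeth requiring endodontic treatment after the first randomization". The abstract agrees.
- **Intervention**, on larger pulp exposures or failed hemostasis: "a root canal treatment is performed, and the case is considered a failure for randomization 1 but not randomization 2".
- **Discussion**, explaining why a nested design replaced a full factorial one: "the impossibility of randomizing the adhesive with endodontic treatment, expected to be more frequent with C excavation".
- **Sample size**: "97 % and 90 % of success is expected for P and C dentin excavation strategies, respectively". The section sets a minimum of 464 patients, based on a two-sided 5% test with more than 80% power and an allowance of 10% for losses by 1 year.

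**The concern.** A tooth root-canal treated at T0 has a known outcome for P versus C (failure) and no value for adhesive. It belongs to the model's stated analysis set, yet it cannot enter a model that has adhesive as a two-level covariate. The article gives no coding for it.

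The affected teeth are not a random subset. All are failures, the failure arises after the first randomization, and the authors expect it more often in arm C. The trial's first hypothesis is that partial excavation leads to less irreversible pulp disease. A fit that leaves these teeth out conditions on part of the outcome and removes one route by which the arms are expected to differ.

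The adjustment is not needed to control confounding. Adhesive is allocated 1:1 after excavation, among the teeth that remain. What is at stake is the modelled P-versus-C estimate, the one that accounts for practitioner clustering and prognostic factors. It could disagree with the Fisher test beside it only because the two use different teeth.

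**Working it through.** **1. Reproduce the plan's figure.** Inputs from Sample size: success 97% (P) and 90% (C), two-sided 5%, power above 80%, 10% loss. Exact enumeration of Fisher's test gives 79.9% power at 208 per arm and 80.1% at 209. Then 2 × 209 / 0.9 = 464.4, in line with the stated 464. The pooled normal formula gives 194 per arm (432 in total after inflation) and the continuity-corrected formula gives 222 per arm (494), so neither matches. The planned size therefore agrees with the unadjusted Fisher test, which needs no adhesive value.

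**2. Effect with every tooth kept.** The failure odds ratio, C against P, is (0.10/0.90) / (0.03/0.97) = 3.59. Chi-square power at 209 per arm is 85%. The tables below use chi-square power as a convenient yardstick; it is not the power of the planned Fisher test.

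**3. Effect when T0 root canal failures leave the fit.** Let rC and rP be the T0 root canal rates. The successes do not change, so

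OR = [(0.10 − rC)/0.90] / [(0.03 − rP)/0.97],

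with about 209(1 − rC) and 209(1 − rP) teeth left. The article gives neither rate. The values below are assumptions.

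| rC | rP | C failures among teeth kept | P failures among teeth kept | OR | Chi-square power |
|---|---|---|---|---|---|
| 2% | 0 | 8.2% | 3.0% | 2.87 | 65% |
| 2% | 1% | 8.2% | 2.0% | 4.31 | 84% |
| 5% | 0 | 5.3% | 3.0% | 1.80 | 20% |
| 5% | 1% | 5.3% | 2.0% | 2.69 | 42% |
| 8% | 0 | 2.2% | 3.0% | 0.72 | 8% |
| 8% | 1% | 2.2% | 2.0% | 1.08 | 5% |

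**4. Direction.** From the formula, the OR falls below 3.59 exactly when rC/0.10 > rP/0.03, that is, when T0 root canals are a larger share of C failures than of P failures. At rC = 2% and rP = 1% the shares are 20% and 33%, and the OR rises. At rC = 5% and rP = 1% they are 50% and 33%, and it falls.

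**5. Does a third level rescue the model?** A level for teeth without adhesive contains only failures. It is predicted perfectly and carries no information on P versus C. In simulation (600 runs per scenario, 209 per arm, no practitioner effect, rP = 0), the median OR with the third level equalled the complete-case one each time:

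| rC | All teeth, no adhesive term | Adhesive, complete cases | Adhesive, three levels |
|---|---|---|---|
| 2% | 3.78 | 3.02 | 3.02 |
| 3.5% | 3.60 | 2.43 | 2.43 |
| 5% | 3.57 | 1.73 | 1.73 |
| 7% | 3.61 | 1.07 | 1.07 |

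**6. How the two planned analyses can part.** With 21/209 failures in C and 6/209 in P, Fisher's p = 0.0045. Remove 10 C failures and 1 P failure as T0 root canals: 11/199 against 5/208 gives p = 0.13.

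**The case against.** Four points can be made for the plan.

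- **The article does not say that these teeth are dropped.** It says the reverse: the model covers everyone with an outcome. This stands. Exclusion is the consequence of a standard fit, not stated text. What the text contains is a conflict between the covariate and the analysis set. An unseen analysis plan might settle the coding, but the article itself fixes the covariate.
- **The main test is intact.** This also stands. Fisher's test is named first, keeps every T0 failure and reproduces the 464. A reader might infer that the primary comparison or its power is compromised; the documents do not support that.
- **The direction is not fixed.** A reader might infer that the model must be biased towards no difference. The Discussion says only that endodontic treatment is expected more often with C, and the working shows that this is not sufficient. The 8% rows also assume that 80% of all C failures are T0 root canals. Nothing in the article supports so high a share, since small exposures with hemostasis are capped and restored.
- **Some codings keep the teeth.** A single indicator (antibacterial adhesive = 1, everything else = 0) retains them without separation. In simulation with no adhesive effect, the P-versus-C odds ratio then stays close to the unadjusted fit, at about 3.6 to 3.8. So the adhesive term does not force the bias. However, the adhesive coefficient then loses its meaning, because unallocated failures sit in its reference group, and the article does not specify this coding.

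The three planned sensitivity analyses do not help. They vary missing outcomes, and here it is a covariate that is missing.

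**Conclusion.** The model is wrong as written: it cannot both adjust on a two-level adhesive arm and include every patient with an outcome. Under the usual ways of fitting it, failures that arise after the first randomization leave the P-versus-C contrast. The defect is confined to the hierarchical model.

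Its size depends on T0 root canal rates that the article does not give. Over the assumed ranges it runs from little loss of power with a larger odds ratio (C 2%, P 1%) to a vanished or reversed effect (C 8%). Attenuation is the likely direction if T0 root canals are concentrated in C, but it is not certain. Conditioning on a post-randomization failure is unsound in either direction. All figures assume the planned 97% and 90%, 209 evaluable teeth per arm, no practitioner effect and no other covariates.

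This should be fixed before analysis. It does not put the Fisher comparison or the sample size in doubt.

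**What to change.** In Statistical methods, delete adhesive arm from the P-versus-C model. State that the model is fitted on every tooth from the first randomization that has an outcome, with root canal treatment at T0 coded as failure. Fisher's test and the model then use the same teeth. Apply the same wording to the 2- and 3-year P-versus-C analyses, which reuse this model.

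Use adhesive, and any excavation-by-adhesive interaction, only in a secondary model restricted to teeth that reached the second randomization, and label it so.

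The cost is analysis wording only. Data collection, randomization and the 464 do not change.

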## Background

Currently, caries management should be based on minimal intervention dentistry concepts [1], including minimally invasive cavity preparations when surgical intervention is required. However, with deep carious lesions, the most commonly used procedure is complete excavation in one step, with hardness to a dental probe used to assess caries excavation [2, 3]. This practice leads to a high risk of pulp exposure and poor prognosis in terms of maintaining pulp vitality [4].

Two alternative options have been proposed to minimize the risks of pulp exposure and postoperative pulpal complications.

The first strategy, chronologically, is the stepwise technique (complete excavation in two steps), with residual carious dentin at the pulpal wall of the prepared cavity left under a temporary restoration placed at the first visit followed by a complete excavation at a second visit (generally 2–6 months later). Clinical surveys have compared the stepwise technique with one-step complete excavation in permanent teeth [5, 6], primary teeth [7], and mixed dentition [8]. Nevertheless, the stepwise technique is time-consuming and costly, and pulp exposure occurs in 15–20 % of cases during the second excavation step [9].

The second approach, more controversial due to a paradigm shift, is partial (incomplete/selective) excavation. The clinical procedure is the same as with the stepwise excavation but without any second procedure. To avoid pulp exposure, carious dentin remains close to the pulp and the cavity is sealed with a definitive restoration. This concept is based on substantial evidence that removal of all carious dentin in deep carious lesions is not required for successful lesion management, provided that the restoration can effectively seal the lesion from the oral environment [10]. Studies have compared stepwise with partial excavation techniques only in permanent teeth [11, 12] or complete excavation in one step with partial excavation essentially in primary teeth [13–17] and mixed dentition [8]. Partial excavation results in lower long-term costs, longer-retained teeth and better pulp preservation than complete excavation (in one or two steps). However, because of high risk of bias within studies, more randomized clinical trials are needed for definitive conclusions [9, 18, 19].

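### The hierarchical model for partial versus complete excavation is adjusted for pulp exposure, which arises after the first randomization and lies on the treatment's own causal path

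*Protocol article*

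**What the plan says.** The Randomization section describes a two-stage minimization with a single list of factors. The list starts with investigator, age group and lesion type, and ends with "location of the lesion (proximal or occlusal) and pulp exposure". It does not say which factors serve which stage, and it adds that patient and cavity characteristics are entered before assignment.

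The Statistical methods section plans two analyses of P versus C at 1 year: an unadjusted Fisher's exact test, and a hierarchical logistic model with a practitioner level. The model is adjusted for adhesive arm and "on prognostic factors accounted for in the minimization scheme". The section later states: "Candidate factors for subgroup analyses are patient age, type of carious lesion (primary or secondary), caries risk, lesion location, and pulp exposure". Interactions of a factor with excavation arm or with adhesive may be considered according to clinical relevance.

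The Intervention section fixes the timing. Lesions that look continuous with the pulp chamber on the bite-wing are not admitted, and the first randomization is done before excavation. Exposure is described as a finding after complete excavation. An exposure above 2 mm² and/or without hemostasis leads to root canal treatment and counts as a failure for the first randomization.

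On complete excavation, the Background says: "This practice leads to a high risk of pulp exposure and poor prognosis in terms of maintaining pulp vitality". It presents partial excavation as the way to avoid exposure.

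**The concern.** A covariate in a model for a randomized comparison should be fixed before that randomization. Pulp exposure is not: the excavation arm influences whether it happens. On the protocol's own account it is one of the ways in which complete excavation leads to failure. Holding it constant removes the part of the P-versus-C difference that passes through exposure, and leaves the part that does not. That is a different question from the primary objective, which asks how the two strategies compare overall.

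The problem is sharper because exposure is partly the outcome itself, since large or bleeding exposures are failures by rule. Splitting P versus C by exposure also compares groups that randomization did not form.

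At stake is the agreement of two analyses of one objective. The Fisher test and the model are both named for the primary objective and would have different targets. Only the model allows for several patients per practitioner, so a discordant model result could not simply be set aside.

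**Working it through.** **1. The plan's own figure.** Inputs from the Sample size section: "97 % and 90 % of success is expected for P and C dentin excavation strategies", a "bilateral test with an alpha risk of 5 % and a power greater than 80" per cent, and "supposing at 1 year 10 % of patients lost to follow-up".

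- Exact power of the two-sided Fisher test at 3% versus 10% failure is 79.9% with 208 per arm and 80.1% with 209 per arm.
- 2 × 209 = 418 evaluable, and 418 / 0.9 = 464.4. This agrees with "A total of at least 464 patients would be needed".
- The pooled normal approximation gives 194 per arm (432 after inflation). With continuity correction it gives 222 per arm (494). Of the versions tried, only Fisher gives 464.

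The sample size therefore rests on an unadjusted comparison, and nothing below changes it.

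**2. Order of events.** Eligibility (no visible continuity with the pulp), then randomization 1, then excavation, then any exposure, then randomization 2. Exposure precedes randomization 2 but follows randomization 1. It is a baseline factor for the adhesive comparison and a post-randomization variable for P versus C.

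**3. Size of the effect on the model.** The protocol gives no exposure rates by arm and no share of the effect that runs through exposure, so both are assumed.

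Let e_C and e_P be the exposure rates, f the share of the 7-point difference carried by exposure, and d the added failure risk when exposed:

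- d = f × 0.07 / (e_C − e_P)
- failure if unexposed: C = 0.10 − e_C × d; P = 0.03 − e_P × d
- failure if exposed: add d

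The overall failure rates stay at 10% and 3%, so the unadjusted failure odds ratio is always (0.03/0.97) / (0.10/0.90) = 0.28.

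Worked case, e_C = 20%, e_P = 3%:

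- f = 1: d = 0.07/0.17 = 0.412. Failure if unexposed is 0.10 − 0.20 × 0.412 = 0.018 in C and 0.03 − 0.03 × 0.412 = 0.018 in P. Within each exposure level the arms are identical, so the adjusted odds ratio is 1.00.
- f = 0.5: d = 0.035/0.17 = 0.206. Failure if unexposed is 0.059 in C and 0.024 in P; if exposed, 0.265 and 0.230. Logistic regression on arm and exposure gives an odds ratio of 0.46.

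Across e_C of 15–30% and e_P of 2–5%, with 209 per arm:

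| Share through exposure | Failure odds ratio, adjusted | Power of the model |
|---|---|---|
| Exposure not in model | 0.28 | about 76–84%, depending on the calculation |
| 25% | about 0.35 | about 56–59% |
| 50% | about 0.46 | about 32–36% |
| 75% | 0.62–0.65 | about 13–15% |
| 100% | 1.00 | 5% or less |

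The unadjusted power is 78% by an expected-data Wald calculation and about 83–84% by simulation. The calculation contains arm and exposure only. It has neither the adhesive term nor the practitioner level of the planned model.

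**The case against.** **The Fisher test has no covariates.** This stands. It comes first in the text, estimates the total effect among patients with an outcome, and is the test on which the trial was sized. A reader might infer that the trial as a whole would report no difference when partial excavation works as hypothesised. The protocol does not support that: only the model and any subgroup analyses by exposure are affected.

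**Exposure was probably meant for randomization 2 only.** This is plausible, since exposure cannot be known at randomization 1, and the single list may be compression for a journal article. It is not shown that exposure was fed into the first minimization, so that part is a matter of reconciling two sections. It does not rescue the model: the Statistical methods section adjusts P versus C on the minimization factors without separating the stages.

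**No exposure-by-arm interaction is fixed.** Correct. The subgroup list holds candidates for both comparisons, and interactions are subject to clinical relevance. The text permits such an analysis of P versus C; it does not commit to one.

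**Full mediation is an extreme case.** Also correct. Success is a composite of five criteria that includes fracture, marginal adaptation and caries recurrence, and smaller exposures with hemostasis are capped and may still succeed. At 25–50% the odds ratio still favours P, though with a clear loss of power.

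**Conclusion.** The point holds for the covariate set of the hierarchical P-versus-C model, which is wrong as written. It conditions a named primary-objective analysis on a consequence of the randomized treatment. The direction of the bias, towards no effect, follows from the protocol's own account of how the two strategies differ.

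The size is illustrative. It depends on assumed exposure rates and an assumed mediated share, and on a model simpler than the planned one. At one quarter mediated, about 20 to 25 points of power are lost (for example 78% to 56–59% by the same expected-data calculation). At one half, power is about a third.

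It would go too far to say that the primary analysis as a whole is compromised or that the sample size is wrong. The Fisher comparison and the 464 stand. The practical risk is a clear Fisher result beside a weak or null model result for the same objective, with no stated way to reconcile them.

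**What to change.** - Restrict the P-versus-C model to factors known before the first randomization: investigator, age group, lesion type and lesion location.
- Use pulp exposure only in the minimization for the second randomization and in the model and subgroups for antibacterial versus traditional adhesive, where it is a genuine baseline factor.
- Exclude exposure from subgroup and interaction analyses of P versus C, and report it by excavation arm as an outcome.
- Reconcile the Randomization and Intervention sections by stating which factors feed which randomization.

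The cost is a few sentences in the protocol or analysis plan, settled before the data are analysed. No data, patients or change in sample size are needed.
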